### Dissemination of results

The results from the different centres will be analysed together, published as soon as possible, and presented at an international conference. Step 1 and step 2 will be published in two separate reports. The Trial Management Group (TMG) will form the basis of the Writing Committee and will advise on the nature of the publication. The names of all investigators will be included in the authorship of any publication. Any authorship policy will be agreed by all investigators before the commencement of the trial. The members of the TSC and DMC will be listed with their affiliations in the acknowledgements or appendix section of the main publication. The funders will have no role in the decision to publish or the content of the publication.

### Ethical approval

The Research Ethics Committees of the London School of Hygiene and Tropical Medicine (6544–01), Botswana MoH HRDC (PPME-13/18/1 Vol IX (6)), PMH IRB (5/79/90a), and the University of Pennsylvania (820127) have approved the protocol. We will not begin any recruitment in any individual centre until local ethical approval has been obtained. Any further amendments will be submitted and approved by each ethics committee.

### Timeline

We anticipate that 60 patients will be enrolled in the study in Botswana and 160 patients in Tanzania over a 2-year period. This is feasible based upon historical numbers of admissions and previous studies at these sites [3, 4, 6].

### Ancillary studies

PK/PD and cost-effectiveness studies will be performed as outlined in this protocol. Cryptococcal isolates will be saved and shared with members of the cryptococcal research community for ongoing phenotypic and molecular epidemiology studies. Blood and CSF samples will be saved for ongoing studies examining the phenotype of the immune response to cryptococcus, and the pathophysiology of immune reconstitution inflammatory syndromes. Blood will also be stored for future studies determining how polymorphisms in immune response genes relate to susceptibility to and outcomes from cryptococcal meningitis. Any samples that require shipment will be in accordance with the local Material Transfer Agreement (MTA) guidelines.

### Quality control and assurance

The study sponsor is St George’s University of London. The sites will be visited at regular intervals in order to monitor the conduct of the trial and ensure that the principles of International Conference of Harmonisation (ICH) good clinical practice (GCP) is being adhered to. These visits will be made by the trial manager/monitor from the sponsoring institution. The frequency of monitoring visits will be according to need but will be at least after recruitment of the first 10 to 15 patients at each site, and after recruitment of 50 % and 100 % of patients (trial closure). If issues arise the frequency of visits will be increased. Site initiation assessments will be conducted at each site prior to trial initiation. The trial manager will visit the sites and ensure that all training (including GCP and protocol-specific training) has been completed, that drug supply and equipment are in place and that all study staff are up to date on the protocol and procedures, and are competent to undertake the roles described for them in the standard operating procedures (SOPs). An external audit by the London School of Hygiene and Tropical Medicine will also be conducted towards the beginning of the trial. Central monitoring will be performed in addition to the on-site monitoring procedures. Cumulative monthly reports (including information on recruitment rates, withdrawals, losses to follow up) will be compiled by the trial manager/statistician and reviewed by the TMG. Bimonthly reports on grade III/IV adverse events (AEs)/serious adverse events (SAEs)/serious adverse reactions (SARs)/suspected unexpected serious adverse reaction (SUSARs) will be compiled by the trial manager/statistician and reviewed by the TMG.

### Data collection and data management

Data will be managed using the Clinical DataFax System (Infectious Diseases Institute, Uganda). The study teams will directly enter data onto paper CRFs that will be labeled with unique patient identifiers. These will be scanned and sent in real time to the DataFax Research Unit, where data entry, verification and review will be performed. Routine quality control checks will be in place that will capture possible inconsistencies/missing data in real time, allowing queries to be sent back weekly to the study teams. Additionally, at monitoring visits the data entered in the CRFs will be checked against available source data by the trial monitor/manager. Trial data will be checked for missing or unusual values (range checks) and checked for consistency. If any such problems are identified, any data that are changed will be crossed through with a single line and initialled. Site investigators will not have access to cumulative data by study arm. On completion of recruitment, data will be securely exported from the DataFax database into the Stata statistical package, and following data cleaning and checking, the database will be locked and analysis will proceed according to the predefined analysis plan.

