**Methodology/design:**

This is an adaptive open-label phase II/III randomised non-inferiority trial comparing alternative short course AmBisome regimens. Step 1 (phase II) will compare four treatment arms in 160 adult patients (≥18 years old) with a first episode of HIV-associated CM, using early fungicidal activity (EFA) as the primary outcome: 1) AmBisome 10 mg/kg day one (single dose); 2) AmBisome 10 mg/kg day one and AmBisome 5 mg/kg day three (two doses); 3) AmBisome 10 mg/kg day one, and AmBisome 5 mg/kg days three and seven (three doses); and 4) AmBisome 3 mg/kg/d for 14 days (control); all given with fluconazole 1200 mg daily for 14 days. STEP 2 (phase III) will enrol 300 participants and compare two treatment arms using all-cause mortality within 70 days as the primary outcome: 1) the shortest course AmBisome regimen found to be non-inferior in terms of EFA to the 14-day control arm in STEP 1, and 2) AmBisome 3 mg/kg/d for 14 days (control), both given with fluconazole 1200 mg daily for 14 days. STEP 2 analysis will include all patients from STEP 1 and STEP 2 taking the STEP 2 regimens. All patients will be followed for ten weeks, and mortality and safety data recorded. All patients will receive consolidation therapy with fluconazole 400–800 mg daily and ART in accordance with local guidelines. The primary analysis (for both STEP 1 and STEP 2) will be intention-to-treat.

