### Schedule

Clinical response will be monitored daily for the first 2 weeks or until discharge (whichever is later), then on follow up at 3, 4, 6 and 10 weeks after the start of therapy. Every effort will be made (e.g., with mobile telephone calls and financial help with travelling expenses) to obtain accurate and complete follow-up data for 10 weeks after the start of treatment. Particular attention will be paid to ascertaining immune reconstitution reactions in ART-naïve patients after starting ART.

Five millilitres of blood will be collected on days 3, 5, 7, 10, 12, and 14 of the study for creatinine and electrolytes. Full blood count (FBC) and alanine transaminases (ALT) will be obtained on days 7 and 14 of the study. On the day of the visit to the study clinic (week 4), blood will be drawn for creatinine, electrolytes, FBC and ALT. An extra 2.5 ml of blood will be taken for PK studies at the time of monitoring blood tests, on days 1 and 3 (excluding the single-dose arm) at the end of AmBisome infusion, and then 3, 6, 8 and 24 h post infusion. Follow-up CSF examinations will be performed on days 3, 7, 14 and 21 to determine opening pressure, quantitative fungal culture (QCC), CSF for drug levels, and immune parameters. In a variation on prior EFA studies (LPs on day 1, 7 and 14), in step 1 LP will be done at day 21 and for day-14 and day-21 quantitative cultures, an extra plate will be spread with 1 ml of undiluted CSF – this will increase sensitivity tenfold, and may help differentiate the duration of the effect of AmBisome on clearance with alternative regimens. Cryptococcal clearance rates will be calculated using a summary statistic for each patient, the rate of decrease in log CFU per ml CSF per day derived from the slope of the linear regression of log CFU against time for each patient. A linear regression model will be used to compare mean rates of decline or EFA for each experimental treatment, giving summary differences with 95 % CI and significance levels. We will adjust analyses for potential confounding factors, including baseline fungal load. Note that follow-up CSF examinations for study purposes in step 2 will be performed on days 7 and 14 only.

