Primary and secondary outcomes for step 1 and step 2 are as listed above. For step 2 the primary endpoint is mortality within the first 10 weeks by treatment arm. The two treatment groups will be compared using the Cochran-Mantel-Haenszel test for categorical data. Patients lost to follow up will be censored in the initial analysis. Sensitivity analysis in which all patients lost to follow up are assumed to have died, and Cox regression time-to-event analysis will be performed.

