### Termination of the study

The trial will be considered closed when the last patient has completed 10 weeks in the study and all follow-up and laboratory reports have been received. Early termination could occur if the DMC decides there is an unacceptable level of adverse events in any of the test arms.

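### The export that feeds database lock and analysis is tied to completion of recruitment, 10 weeks before the last patients' Step 2 primary endpoint can be known, and this conflicts with the protocol's own definition of trial closure

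*Protocol article*

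**What the plan says.** The section on data collection and data management names one milestone for creating the analysis dataset: "On completion of recruitment, data will be securely exported from the DataFax database into the Stata statistical package". The same sentence goes on: "following data cleaning and checking, the database will be locked and analysis will proceed according to the predefined analysis plan". It mentions neither completed follow-up nor a later export.

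The section on quality control and assurance uses the recruitment milestone in the same way. It schedules monitoring visits "after recruitment of 50 % and 100 % of patients (trial closure", so full recruitment is labelled as closure of the trial.

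Three other places use the follow-up milestone:
- The termination section says: "The trial will be considered closed when the last patient has completed 10 weeks in the study and all follow-up and laboratory reports have been" (the quoted sentence ends by requiring their receipt).
- Abstract, methodology: "All patients will be followed for ten weeks, and mortality and safety data recorded".
- Schedule: every effort will be made "to obtain accurate and complete follow-up data for 10 weeks after the start of treatment".

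The section on type of analysis states: "For step 2 the primary endpoint is mortality within the first 10 weeks by treatment arm". The arms are compared with a Cochran-Mantel-Haenszel test. Patients lost to follow-up are censored in the initial analysis and assumed dead in a sensitivity analysis. Cox regression is also planned.

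**The concern.** A death-within-10-weeks endpoint is settled for a patient only at death or at 10 weeks. On the day the last patient is enrolled, anyone enrolled in the preceding 10 weeks and still alive has neither. The stated export trigger and the stated closure condition lie at least 10 weeks apart, and the data management sentence links the first of them to lock and analysis.

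If the sentence were applied literally, the consequences would depend on how unfinished patients were handled. Counting them as alive understates mortality in both arms and shrinks the absolute difference. In a non-inferiority comparison, that makes it easier to accept a worse regimen. Dropping them costs power. Dropping only the unfinished survivors while keeping the known deaths would overstate mortality in both arms. The trial is open-label, which is a further reason to fix the data cut for the primary endpoint unambiguously in advance.

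**Working it through.** **The plan's own figure.** Inputs from the sample size section for Step 2: mortality 25 % in both arms, margin 15 points, one-sided alpha 0.025, power 90 %.

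n per arm = 2 × 0.25 × 0.75 × (1.960 + 1.282)² / 0.15² = 175.1, rounded up to 176. This matches the stated 176, and 176 − 40 = 136 also matches. With 150 new patients and 40 from Step 1, 190 per arm (380 in total) are analysed. Power at 190 per arm is Φ(0.15/√(2 × 0.1875/190) − 1.96) = 92.2 % before losses.

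**How many patients would be unfinished at the last enrolment.** With 300 new patients enrolled evenly over T weeks, 300 × 10/T were enrolled in the last 10 weeks. T is not given for Step 2. The only accrual figure is in the timeline section ("60 patients will be enrolled in the study in Botswana and 160 patients in Tanzania over a 2-year period"), which is 220/104 = 2.1 per week and covers two countries, whereas Step 2 adds sites. At that rate, 300 patients take 142 weeks. A 52-week period is assumed as the fast end. Deaths among these late patients are already determined, so the counts below are slight upper bounds.

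**If all of them were dropped.** n per arm = 190 − (300 × 10/T)/2, and power = Φ(0.15/√(0.375/n) − 1.96).

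**If all of them were counted as alive unless already dead (an assumption; the article does not say this).** Take true rates exactly at the margin, 25 % against 40 %, with 190 per arm. Follow-up of the unfinished patients is uniform over 0-10 weeks. Death times follow either a constant hazard or a front-loaded pattern (exponential, rate 3 per 10 weeks, among those who die by week 10). The average mortality seen in unfinished patients is then 13.1 % and 21.7 % (constant hazard) or 18.0 % and 28.8 % (front-loaded). With s the unfinished share, observed mortality = (1 − s) × true rate + s × that value. The false non-inferiority rate is Φ((0.15 − observed difference)/SE − 1.96). In the last two columns the front-loaded result comes first.

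| Assumed T (weeks) | Enrolled in last 10 weeks | Share of 380 | n per arm if dropped | Power if dropped | Apparent difference (points) | False non-inferiority |
|---|---|---|---|---|---|---|
| 52 | 58 | 15.2 % | 161 | 87.5 % | 14.4 or 14.0 | 3.4 or 4.0 % |
| 78 | 38 | 10.1 % | 171 | 89.3 % | 14.6 or 14.4 | 3.1 or 3.4 % |
| 104 | 29 | 7.6 % | 176 | 90.1 % | 14.7 or 14.5 | 2.9 or 3.2 % |
| 142 | 21 | 5.6 % | 179 | 90.7 % | 14.8 or 14.6 | 2.8 or 3.0 % |

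Example at T = 52 with constant hazard: s = 57.7/380 = 0.152. Observed rates are 23.2 % and 37.2 %, difference 14.03 points, SE = √((0.232 × 0.768 + 0.372 × 0.628)/190) = 4.66 points, and Φ(0.97/4.66 − 1.96) = 4.0 %.

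Dropping unfinished patients keeps at least 176 per arm only if 3000/(2T) is at most 14, that is, if T is about 107 weeks or longer, before any other loss.

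**The case against.** The strongest reply is that the article never says anyone will be analysed with unfinished follow-up. The data management sentence dates only the export. Lock comes after cleaning and checking, for which no date is set. The abstract, the schedule and the termination section all commit to 10 weeks for everyone. On this view, completion of recruitment is loose shorthand for the end of the trial, as the monitoring section's label suggests. This reply largely stands as a forecast of what the trial team would do. A reader might infer that the last patients will enter the mortality analysis incomplete, but the documents support this only as what would follow if the sentence were applied literally. The reply does not remove the inconsistency: the only sentence leading to lock and analysis names a milestone that comes too early for the primary endpoint.

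A second reply is that rules for lock and for administratively incomplete follow-up belong in the analysis plan, which is not shown. That is right, and the absence of such a rule is not held against the article. The point is that the milestone stated here is wrong.

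A reader might also infer a much larger effect by assuming that Step 2 finishes within the same two years as Step 1. Step 1 would take 160/2.115 = 75.6 weeks, leaving 28.4 weeks for 300 patients, and 28 % would be unfinished. That needs 300/28.4 = 10.6 patients per week, five times the only accrual rate in the article. The timeline section does not say that Step 2 ends within those two years. Equally, it cannot be said in general that power would fall below 90 %: at the article's own rate, dropping the unfinished patients leaves 179 per arm and 90.7 %.

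**Conclusion.** The point holds as a wrongly stated milestone and an internal inconsistency. The data management and quality control sections use completion of recruitment, while the termination section and the endpoint itself require 10 weeks more. Followed as written, the export would leave about 5.6 % (142-week accrual) to 15 % (52-week accrual) of 380 patients without a determined Step 2 primary endpoint. Under the counted-as-alive assumption the false non-inferiority rate would be 2.8-3.0 % to 3.4-4.0 % instead of 2.5 %. If these patients were dropped, power would be 90.7 % down to 87.5 %. These sizes rest on assumed accrual periods, even enrolment and two assumed death-time patterns. They are modest, and they disappear if the team waits for the last 10-week visit, as other sections imply it would.

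**What to change.** In the data management section, replace the opening milestone with the termination condition. For Step 2, export, lock and analysis take place when the last randomised patient has completed 10 weeks of follow-up or has died, and all follow-up and laboratory reports have been received. In the quality control section, separate the visit at full recruitment from closure of the trial, so that closure has one meaning throughout.

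For Step 1, export for the EFA analysis once the last scheduled CSF culture of the last Step 1 patient has been reported. Export for the 10-week mortality outcomes once the last Step 1 patient has completed 10 weeks.

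The cost is a few words in two sections. No extra patients or visits are needed, and the final analysis waits only as long as the termination section already requires.

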### Confidentiality

The principles of the UK Data Protection Act will be followed regardless of the countries where the trial is being conducted. The study site records will contain names, addresses, and contact details of the patients to enable follow up of patients. Unique numeric identifiers will be assigned to all patients, and only this unique number will be included in data sent from the trial sites and entered into the study database. The site investigator will ensure safekeeping of the patient data.

### Termination of the study

The trial will be considered closed when the last patient has completed 10 weeks in the study and all follow-up and laboratory reports have been received. Early termination could occur if the DMC decides there is an unacceptable level of adverse events in any of the test arms.

### Indemnity

The sponsor of the trial is St George’s University of London. All personnel involved in the trial will be expected to be indemnified by their employing authority. Patients will be indemnified through the policy of the trial sponsor. Local insurance will be taken out where local regulations require this.

## Discussion

The potential impact of a safe, sustainable regimen of high-dose intermittent AmBisome of equivalent efficacy to 2 weeks of daily Amphotericin-based induction (either conventional or liposomal), would be to reduce 10-week mortality in the majority of the African centres that still rely on fluconazole monotherapy, from approximately 60 % [5, 6, 14] to the 20−40 % seen with Amphotericin B-based combinations [2, 3]. It would also facilitate effective treatment, reduce the duration of hospital admissions, and lower the high burden of drug-related side effects currently seen in centres using conventional AmB-d based therapy. A large reduction in the number of doses, and duration of hospitalisation, together with reduced pricing of AmBisome, may result in costs that are comparable, or less than 2 weeks conventional AmB-d being given with appropriate monitoring.

## Abbreviations

ALT: Alanine transaminases
AmB-d: Amphotericin B deoxycholate
AmBisome: Liposomal amphotericin B
ART: Anti-retroviral therapy
CFU: Colony-forming units
CRF: Case report form
CSF: Cerebrospinal fluid
DMC: Data Monitoring Committee
EFA: Early fungicidal activity
FBC: Full blood count
GCP: Good clinical practice
HRDC: Human Research and Development Committee
ICH: International Conference on Harmonisation
IRB: Institutional review board
iv: Intravenous
LP: Lumbar puncture
MoH: Ministry of Health
PD: Pharmacodynamics(s)
PK: Pharmacokinetic(s)
PMH: Princess Marina Hospital
SAE: Serious adverse event
TMG: Trial Management Group
TSC: Trial Steering Committee
